# Protocol of the LEONORA randomized clinical trial: Lower gastrointestinal symptom burden by prophylaxis with synbiotics after colorectal cancer surgery

**DOI:** 10.1186/s12885-026-15903-9

**Published:** 2026-03-25

**Keywords:** Randomized controlled trial; synbiotics, Inulin, Colorectal cancer, Quality of life, Gut microbiome, Infections, Inflammation, Metabolites

## Abstract

**Background:**

A key component of colorectal cancer (CRC) treatment is the surgical resection of the tumor, accompanied by antibiotic treatment and often chemotherapy, which severely alter the gut function and its microbiome. Thus, CRC patients commonly suffer from gastrointestinal symptoms like chronic diarrhea, which can persist in some patients for several years.

Synbiotics are a mixture comprising live microorganisms and substrate(s) selectively utilized by host microorganisms that confer a health benefit on the host. Previous randomized controlled trials have shown that synbiotics reduce rates of post-operative infections and related complications, diarrhea incidence, and inflammation. However, data on the gastrointestinal quality of life are very sparse.

**Methods:**

The proposed LEONORA trial is a randomized controlled trial with 206 CRC patients, who shall be recruited in 10 German clinics. While 103 patients in arm 1 will receive a placebo, 103 patients in arm 2 will be given a daily synbiotic treatment for 12 weeks with 50 billion colony-forming units of 12 live bacterial strains. After the wound healing phase, patients in the intervention arm will additionally receive the dietary fiber inulin from weeks 5 to 12. Every 2 weeks, the inulin dosage will be stepwise increased from 3 g to 10 g per day to slowly train the gut microbiome and avoid flatulence. The study participants in the placebo group, on the other hand, receive maltodextrin as a second placebo, which is very similar to inulin in appearance and taste, but does not affect the gut microbiome.

The primary endpoint is the gastrointestinal quality of life 90 days after surgery. Further outcomes include rates of infections, cancer recurrence, cancer survival, blood-based inflammatory biomarkers, and metabolites. Stool samples will be collected to additionally address changes in the gut microbiome and metabolome composition.

**Discussion:**

The 3-month therapy with synbiotics could be a well-tolerated and very cost-effective approach to increase the gastrointestinal quality of life of CRC patients. Thus, the results of the proposed LEONORA trial will be of high relevance for both caregivers and CRC patients.

**Trial registration:**

German Clinical Trials Register (DRKS): DRKS00034919, November 21, 2024; https://www.drks.de/search/de/trial/DRKS00034919.

**Supplementary Information:**

The online version contains supplementary material available at 10.1186/s12885-026-15903-9.

## Background

The key components of most colorectal cancer (CRC) treatments are the tumor resection, accompanied by perioperative antibiotic prophylaxis. Furthermore, the surgery is followed by adjuvant chemotherapy for specific subgroups of CRC patients. Following CRC resection, disorders in the gastrointestinal tract are often believed to be a temporary issue for about 3–6 months after surgery. However, a substantial proportion of patients still reports symptoms 1 year after their cancer diagnosis with respect to pain (43% of patients), constipation (31%), and diarrhea (31%) [1]. Moreover, chronic diarrhea has been reported by 13–50% of CRC survivors up to 10 years after treatment [2]. In comparison to the general population, CRC survivors more often report suffering from impaired physical quality of life, with bowel problems being very common [3].

Synbiotics can be defined as “a mixture comprising live microorganisms and substrate(s) selectively utilized by host microorganisms that confers a health benefit on the host” [4]. The live microorganisms, also called “probiotics”, can beneficially affect the host by improving the composition and the equilibrium of the bowel microbiota [4]. The substrates, also called “prebiotics”, are non-digestible fibers that reach the colon and serve as a substrate for fermentation by probiotics and indigenous colonic bacteria, providing nutrients important for host health [4]. Synbiotics were found to be more effective than the administration of probiotics alone [5]. Current literature provides no evidence of an increased risk of complications with probiotics supplementation in humans [6].

Preliminary evidence from cell culture, animal studies, and first observational human studies suggests that probiotics and prebiotics have anti-carcinogenic and potentially cancer therapy-enhancing effects [7–9]. Moreover, an increasing number of studies suggest an association between the intestinal microbiota composition and oncogenesis and response to anti-cancer treatment [10]. It has been observed that the efficacy of certain anticancer agents depends on the prevalence of distinct bacterial groups in the gut microbiome, which may be negatively affected by antibiotics [8].

Recently published meta-analyses, summarizing the effects of 14–19 randomized controlled trials (RCTs) with pro- or synbiotics administration in CRC patients, consistently concluded that such treatments reduce post-operative infections, related complications, and the incidence of diarrhoea [11–15]. They led to a faster return to a normal gut function, shortened postoperative antibiotics use, lowered the incidence of sepsis, and shortened the length of hospital stay [11, 12]. Furthermore, anti-inflammatory effects have been documented by decreased C-reactive protein and interleukin-6 levels [16].

In order to avoid conducting a trial that was already done, we searched MEDLINE, Cochrane Central, the Cochrane Library, and clinicaltrialsregister.eu, DRKS, clinicaltrials.gov, and ICTRP on September 25, 2023, for RCTs aiming to demonstrate the effects of probiotic or synbiotic therapy on the quality of life of CRC patients. The trial of Theodoropoulos et al. [17] is the only previous or registered trial that tested/tests the efficacy of synbiotics on the gastrointestinal quality of life among CRC patients shortly after tumor surgery. The LEONORA trial will extend the evidence from the study of Theodoropoulos et al. [17] by the following aspects:More diverse probiotic formulation (7 Lactobacillus, 4 Bifidobacterium, and 1 Streptococcus bacterial strain vs. 4 Lactobacillus bacterial strains).More potent prebiotic (10 g inulin vs. a mix of 2.5 g of inulin with 7.5 g of less potent fibers (β-glucan, pectin, and resistant starch) [18].Longer therapy (90 vs. 15 days).Multi-center approach embedded in the German routine clinical setting instead of a single-center study from Greece.A much larger sample size (*n* = 206 instead of *n* = 67).

With 206 patients, the LEONORA trial would be the largest placebo-controlled RCT worldwide to be conducted on the efficacy of synbiotics in the prevention of postoperative complications in CRC patients. Moreover, the LEONORA trial would be the first on this topic from Germany specific for CRC patients. The only 3 previous studies from Germany included pancreatic cancer patients or heterogeneous cancer populations [19–21]. In addition, it would be the first trial worldwide looking into the effects of synbiotics on the emergence of multidrug-resistant organisms. Furthermore, stool samples will be collected to ascertain changes in microbiota composition. Due to the low case numbers and short follow-up times, all meta-analyses on cancer survival were inconclusive [11–15]. Thus, having another large trial with several years of mortality follow-up time might lead to a statistically significant pooled effect estimate for cancer survival in future meta-analyses.

### Aims of the study

The main objective of this study is to test whether the early post-surgical administration of synbiotics has an impact on the gastrointestinal function-related quality of life 90 days after surgery. Further objectives are to test the efficacy of the intervention on rates of infection, inflammatory biomarkers, and recurrence-free survival. Stool samples will be collected to additionally address changes in microbiota composition.

## Methods/Design

### Study design

The LEONORA study is a national, multicenter, prospective, double-blinded, randomized, controlled, phase-III trial. Figure 1 shows the schematic flow-chart of the study design. This trial protocol follows the SPIRIT 2025 Checklist for the reporting of protocols of RCTs (Table S2, Supplemental Material).

**Fig. 1 Fig1:**
[figure not shown]
Design of the LEONORA study. Abbreviations: CRC, colorectal cancer

#### Intervention

The intervention group will receive a commercially available probiotic and prebiotic preparation for daily use for 12 weeks, i.e., 84 days, starting on the first day after surgery, at which oral liquid diet is being tolerated (Day 1–3 post surgery).

The probiotic treatment is Essential-Biotic^®^ Complete delayed-release capsules (Allergy Research Group, CA, USA), which shall be taken once daily. One capsule contains 50 billion colony-forming units (CFU) of 12 different bacterial strains from the Bifidobacterium, and Lactobacillus families, as well as Streptococcus thermophiles.

Multiple-strain probiotics have been suggested to be more effective than single-strain probiotics [22]. The amount of 50 billion CFU probiotic cells is in the middle of the used probiotics of previous trials, which ranged from 3 to 100 billion CFU in most studies [23]. The current literature provides no evidence of an increased risk of complications with probiotics supplementation in humans [6].

The prebiotic treatment is 10 g/day of the fermentable fiber inulin made from chicory plants (Orafti^®^ Synergy1 powder, BENEO GmbH, Mannheim, Germany). This dose is the median dose of 10 previous trials using inulin as part of a synbiotic and administered to patients after oncologic surgery [23]. The coordinating center will fill the daily doses in sachets, whose powder content shall be dissolved in a drink by the study participants. The drink shall be used to swallow the capsule with the probiotic after a meal to reduce the contact with gastric acid.

Flatulence is a common and dose-dependent adverse event of inulin doses ≥ 5 g/day but a tolerance was observed after 2 weeks of use, presumably by microbiota adaptation to the increased fiber availability [24]. To exclude a risk of flatulence during the wound healing phase in the first 4 weeks after surgery, inulin intake will start from week 5 on. The inulin treatment shall start in week 5–6 with 3 g/day, which is the minimal possible dose with a shown effect on microbiota abundance while there is no risk of flatulence, and be continued with 5 g/day in week 7–8 when tolerance towards the very low dose of 3 g is achieved [24]. After intake of 7 g/day in week 9–10, the full dose of 10 g/day shall be applied in week 11–12. The chosen prebiotic and probiotic will act together as a synbiotic because inulin is a specific substrate for the bacteria of the Bifidobacterium family and, to a lesser extent, the Lactobacillus family [18, 25].

#### Control

The control group will receive two different placebos. Using a placebo as the comparator is ethically feasible because synbiotics or probiotics are not part of routine care in German hospitals after CRC resection. The placebo for the probiotic capsule with live bacteria will be a capsule in the same appearance filled with Füllstoff DAC, which is mannitol 35 - a sugar with no effects on microbiota. The placebo for the prebiotic inulin will be maltodextrin powder, which is a sugar with no effects on microbiota, which has the same appearance and almost the same weight, sweet taste, and solubility in water as inulin. The maltodextrin powder will be filled in the same sachets as the inulin powder. Most previous trials testing the effects of inulin on microbiota used maltodextrin powder as the placebo and observed no changes in microbiota in the control group [25].

#### Blinding

The Pharmacy of the University Clinic Heidelberg (Pharmacy) will overcapsule the probiotic with neutral capsules and manufacture the placebo capsules for the probiotic. All probiotic verum and probiotic placebo capsule packages will be labeled with randomization numbers (RandomID) by the Pharmacy obtained from the randomization list.

An office assistant in the coordinating center will weigh the prebiotic intervention (inulin powder) and its placebo (Maltodextrin powder), will fill them in sachets, create packages per study participant containing either inulin or placebo sachets, label them accordingly, and bring them to the Pharmacy. The Pharmacy will label these packages with the randomization numbers (RandomID) and will remove other labels, which could lead to the identification of the randomization group. An office assistant from the coordinating center will fetch the packages for the probiotic/placebo and prebiotic/placebo for each randomization number from the Pharmacy, pack them together, and send these packages to the recruiting study centers. The randomization list will only be kept in the Pharmacy until the trial and statistical analysis are completed. Thus, a triple blind study will be conducted because the study participants, the study physicians/data collectors in the coordinating center, and the trial statistician will not know which study participant received verum and which received placebo.

In case of the need for emergency unblinding (only situations in which it is medically necessary to know the patient’s treatment), the study physician can open a sealed envelope with information about the status (verum or placebo) of the study participant, which will be stored at the study center. Any emergency unblinding must be documented in the eCRF and has to be reported without delay to the coordinating center by the study physician. As such, blinding will remain intact for all other study participants.

#### Randomization

Computer-generated randomization lists to randomize the study participants 1:1 to the intervention and control group will be prepared by the Pharmacy, which will be stratified by recruiting center and cancer location (colon or rectum) using blocks of 2 randomization numbers (RandomIDs) per package, which always contain 1 verum and 1 placebo. The RandomIDs will start with either the letter “K” for colon or “R” for rectum cancer patients and end with a number between 1 and 199 (i.e., K001-K199 and R001-199). If a patient has both colon and rectum cancer, he or she will get a RandomID with a “K”. The coordination center will take care and document that always a block of 2 packages per cancer entity (e.g., RandomIDs K001 and K002 or RandomIDs R001 and R002) are distributed to one center. The RandomIDs will be used to label the study drug packages, informed consent forms, questionnaires, blood sampling kits, stool sampling devices, and all other study materials to be send to the recruiting centers.

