#### Study centers

The study will be conducted on a national multicenter basis. The coordinating center is the Division of Clinical Epidemiology of Early Cancer Detection, German Cancer Research Center, Heidelberg. Recruitment is planned to be conducted within 2–3 years in 10 German hospitals in the following towns: Cologne, Heidelberg, Berlin, Essen, Augsburg, Tübingen, Gießen, Stuttgart, Erlangen, and Frankfurt am Main (see Supplemental Material for the institution’s names). The coordinating center will create packages with all study materials and trial drugs needed for a study participant, which are all labelled with the randomization ID (RandomID), which will be supplied by the Pharmacy of the University Clinic Heidelberg, which has the randomization list. The study centers will assign these RandomIDs consecutively to the patients in the timely order of study inclusion and document the RandomID together with the study participants’ name and date of birth in the eCRF.

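### With fixed blocks of 2, opening one emergency envelope discloses the block partner's arm, so the statement that blinding stays intact for all other participants is false for that partner

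*Protocol article*

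**What the plan says.** Three sections of the protocol article bear on this.

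- **Randomization.** Lists are 1:1, prepared by the Pharmacy and stratified by recruiting centre and by colon versus rectum, "using blocks of 2 randomization numbers (RandomIDs) per package, which always contain 1 verum and 1 placebo". The coordinating centre ensures and documents that "always a block of 2 packages per cancer entity (e.g., RandomIDs K001 and K002 or RandomIDs R001 and R002) are distributed to one center".
- **Study centers.** "The study centers will assign these RandomIDs consecutively to the patients in the timely order of study inclusion".
- **Blinding.** When it is medically necessary, "the study physician can open a sealed envelope with information about the status (verum or placebo) of the study participant". The envelope is kept at the study centre. The event is entered in the eCRF and "has to be reported without delay to the coordinating center by the study physician". The paragraph concludes: "As such, blinding will remain intact for all other study participants".

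The article mentions neither varying block sizes nor keeping the block size from the sites.

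**The concern.** A block of 2 with one package of each kind leaves no uncertainty once either member is known. Adjacent numbering, shipment of whole pairs and consecutive use also make the pair recognisable at the site. So the envelope that unblinds one participant unblinds a second, contrary to what the Blinding section says.

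Two things are at stake. First, masking of the partner at the site is lost. It is also lost at the coordinating centre if the report or eCRF entry there shows the arm. That centre documents the pairs, mails and receives the day 30 and day 90 questionnaires, and telephones participants whose compliance is unclear. The Blinding section counts its data collectors among the blinded. Second, if the partner has not been enrolled, the next allocation in that stratum is known in advance. One exclusion criterion rests on the investigator's opinion, so foreknowledge could affect who is entered. The primary endpoint is a self-reported score, which makes masking and concealment worth protecting.

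**Working it through.** **Inputs from the article.** Block size b = 2 with one of each arm; 1:1 allocation; strata are centre by cancer location; 206 randomized; 10 hospitals; recruitment over 2 to 3 years. The planned number reproduces: 154 / (1 − 0.25) = 205.3, which rounds up to 206. That makes 103 pairs if all are completed. Block size does not enter the sample size, and no stated figure is disputed.

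**1. What one opened envelope discloses.** In a block of size b with b/2 per arm, the probability that a given other member is in the opposite arm, once one member is known, is (b/2)/(b − 1).

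| b | Calculation | Probability |
|---|---|---|
| 2 | 1/1 | 100% |
| 4 | 2/3 | 66.7% |
| 6 | 3/5 | 60.0% |

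Under the plan, disclosure of the partner is certain.

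**2. Who is exposed.** Take K001 and K002. If K001 is unblinded, the exposed participant is K002, the next colon patient at that centre. If K002 is unblinded, it is K001, who is already enrolled. Participants in other blocks are unaffected. Concealment is lost only in the first case, and only if K002 has not yet been assigned.

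**3. How many.** The article gives no unblinding rate. If k envelopes are opened at random among 206 participants in complete pairs, the expected number of further participants exposed is k × [1 − (k − 1)/205]. The values of k are illustrative.

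| k | Further exposed | Total known |
|---|---|---|
| 1 | 1.0 | 2.0 |
| 5 | 4.9 | 9.9 |
| 10 | 9.6 | 19.6 |

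**4. The ceiling.** Half of all allocations (103 of 206) are fully determined by the one before, but this applies only if every first allocation is known. For blocks of 4 and 6 the corresponding shares are 33.3% and 25%.

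**5. Could the partner still be unenrolled?** If 10 centres × 2 locations accrued equally (an assumption), each stratum would have 206/20 = 10.3 patients. That is one every 104/10.3 = 10.1 weeks over 2 years, or every 156/10.3 = 15.1 weeks over 3 years, against a 12-week treatment period. An envelope opened during the first member's treatment could therefore precede the second member's enrolment. Real accrual will be uneven.

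**6. Effect of mixed blocks of 4 and 6 with hidden boundaries.** On average, one block of 4 and one of 6 give 10 adjacent pairs of positions: 3 inside the block of 4 (opposite with probability 2/3), 5 inside the block of 6 (3/5) and 2 across a boundary (1/2). So (3 × 2/3 + 5 × 3/5 + 2 × 1/2)/10 = (2 + 3 + 1)/10 = 60%. A simulation of one million allocations gave 60.1%.

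**7. Cost in balance.** Assume 20 strata with random (Poisson) sizes averaging 10.3. After k of b allocations the imbalance within a block has variance k(b − k)/(b − 1). Averaged over positions this is 0.5 for b = 2, 0.833 for b = 4 and 1.167 for b = 6. Weighting by block length, the 4/6 mix gives 0.4 × 0.833 + 0.6 × 1.167 = 1.033. The mean absolute difference in arm totals is about √(2/π) × √(20 × variance).

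- Blocks of 2: 0.798 × √10 = 2.5
- Blocks of 4/6: 0.798 × √20.7 = 3.6

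Simulation gave the same means, with 95th percentiles of 6 and 9.

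**The case against.** The strongest reply concerns reach. Emergency unblinding is limited to medical necessity, and the article expects no serious adverse events related to the trial medication, so few envelopes may be opened. The patient completes the primary endpoint questionnaire, and nothing tells a patient who the block partner is; a physician's inference does not by itself unblind the person reporting. Disclosure also requires knowing the block rule. The first two points stand and limit the consequence. The last gives little comfort, because the rule is published and the pairs arrive with adjacent numbers.

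A reader might go further and infer that guessing one participant's arm, from flatulence or from a placebo powder that is not quite identical, equally reveals the partner. The documents do not support that. A guess carries over only its own certainty. Inulin starts in week 5 at a dose the article describes as free of flatulence risk and is raised in two-week steps. Daily site monitoring ends at discharge, and questionnaires and diaries go to the coordinating centre, so enrolling staff may never hear of such symptoms. Each participant receives only one powder. This route is secondary and speculative.

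Larger blocks also do less against someone who already knows every earlier allocation. Expected correct guesses, [b/2 + 2^(b−1)/C(b, b/2) − 1/2]/b, fall only from 75% (b = 2) to 70.8% (b = 4) and 68.3% (b = 6). The main gain is for the opened envelope, where certainty is removed.

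**Conclusion.** The sections contradict each other. With the block rule as fixed, the statement in the Blinding section is false for one further participant whenever an envelope is opened and the partner number has been or will be assigned. This follows from the article's own rules and needs no outside assumption except that the person concerned knows the published rule. If the partner is still to be enrolled, concealment of that allocation fails too.

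The size depends on the number of unblindings, which is not stated: at most one extra participant per envelope. It would be wrong to read this as half the trial being unblinded; 103 of 206 is a ceiling that requires every first allocation to be known. The point should be fixed, but it does not by itself invalidate the design or the sample size.

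**What to change.** 1. **Packages not yet shipped.** Have the Pharmacy generate new centre-by-location lists with randomly varying larger blocks, for example 4 and 6. Do not disclose the sizes to sites or the coordinating centre, and ship without recognisable pairs.
2. **Blinding section.** Replace the closing sentence with an accurate one: for packages issued in pairs, unblinding one participant can disclose the block partner.
3. **Pairs already issued.** The first participant was included in September 2025, so some pairs may be in use. Record the partner of any unblinded RandomID as potentially unblinded, with dates showing whether the partner was already enrolled. Add a sensitivity analysis of the primary endpoint that excludes both members.

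**Cost.** A new Pharmacy list and a short amendment. Packing and shipping must also change, because the coordinating centre now distributes and documents pairs, and larger blocks need more packages per stratum. The mean absolute difference in arm totals rises from about 2.5 to about 3.6 patients under the assumptions above. No additional patients are needed.
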